#### Mediation measures

To further understand how the intervention may affect behaviour change, self-efficacy, perceived importance, and know-how (or possessed skills) of and for behaviour change [46–50] will be measured. These measures will be used to estimate to which degree the total effect of the intervention is mediated through these factors. Confidence, importance, and know-how will be measured by asking “How confident are you that you will be able to change your lifestyle?”, “How important do you think it is to change your lifestyle?” and “How well do you know how to change your lifestyle?” all three will have response options on a 10-point scale. We decided not to use validated measure of these three constructs to reduce participant burden, as attrition is problematic in general for digital intervention studies and in particular for this population.

#### Exploratory measures

Apart from the primary, secondary and mediation measures, the trial will also explore the acceptability of the intervention, and the reactions and actions of participants allocated to the control group. Acceptability will be measured using a five-item questionnaire regarding the experience of receiving support (intervention group only, please see Additional file 1). These five items measure participants’ view on perceived support received, specific components of the novel intervention, and if they would recommend the intervention to others. These we found could not be captured with validated measure of acceptability or usability such as the intervention appropriate measure [51] or system usability scale [52]. The two-item questionnaire capturing the control group’s reactions and actions was chosen to reduce participant burden and based on questions we have used in previous trials [13, 33, 53].

#### Follow-up

Follow-ups will be initiated by sending text messages to participants with hyperlinks to questionnaires at 2 and 4 months after randomisation. In all cases, the following attempts will be made to collect data:
A total of two reminders will be sent 2 days apart to those who have not responded.If there is no response given, we will attempt to call participants to collect responses for the primary outcome measures only. A maximum of 5 attempts will be made

### Statistical analysis

Analyses will be done keeping participants within the groups to which they were randomised. Analyses will be conducted using both available data and missing data imputed (multiple imputation with chained equations). We will conduct attrition analyses to explore the missing at random (MAR) assumption underlying these analyses. First, if data is missing systematically then it may be the case that early responders differ from non-responders, and in extension that late responders are more like non-responders. Therefore, one analysis will regress primary outcomes against number of attempts to collect follow-up before a response was recorded. Second, we will investigating if responders and non-responders are different with respect to baseline characteristics.

Data will be graphically examined for outliers or data input errors, and sensitivity analyses will be performed excluding any erroneous data points.

Longitudinal data will be analysed using multilevel models with adaptive intercepts (per individual) and time by group interactions. Bayesian inference will be used to estimate the parameters of the models [54–57] with standard normal priors. For each group by time coefficient, we will report the marginal posterior probability of effect, and the median will be used as a point estimate of the magnitude of the effect. We will also report 50 and 95% compatibility intervals. We will complement the Bayesian analyses with maximum likelihood estimates and null hypothesis test at the 0.05 significance level. Both Bayesian and maximum likelihood estimates will be used for scientific inference.

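### Neither of the two attrition checks reliably probes departures from MAR that differ by arm, although MAR underlies both planned analyses and the arm contrast is the target.

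*Protocol article*

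**What the plan says.** Protocol article, *Statistical analysis*: "Analyses will be conducted using both available data and missing data imputed (multiple imputation with chained equations"). The next sentence names the shared assumption: "We will conduct attrition analyses to explore the missing at random (MAR) assumption underlying these analyses". Two checks follow.

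- **Attempts check.** On the reasoning "in extension that late responders are more like non-responders", one analysis will "regress primary outcomes against number of attempts to collect follow-up before a response was recorded". No arm term or arm-by-attempts term is given.
- **Baseline check.** The second looks at "if responders and non-responders are different with respect to baseline characteristics".

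The same section makes the group-by-time coefficient the quantity reported. The one sensitivity analysis it names concerns data errors: "sensitivity analyses will be performed excluding any erroneous data points".

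*Follow-up* describes a text message with a web link, then two reminders. If there is still no answer, "we will attempt to call participants to collect responses for the primary outcome measures only". *Randomisation* says that participants know their condition, *Control* that controls wait 4 months for the intervention, and *Power calculations* that 25% attrition is assumed.

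**The concern.** The trial reports a contrast between arms, so the departures from MAR of most interest are those that differ by arm. They are plausible here: participants know their allocation and controls are waiting for the product. Neither check, as described, is directed at such differences.

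The baseline check looks at observed variables. Differences between responders and non-responders on these are compatible with MAR, and their absence does not favour MAR over MNAR. The check bears on MCAR and on which predictors the imputation needs.

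The attempts check estimates one slope among responders. If lateness goes with better outcomes in one arm and worse in the other, the slopes can cancel. If only those who never respond differ, responders carry no trace of it. High attempt counts are also telephone answers given to a person, so a slope may reflect mode of reporting and not lateness.

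At stake is whether unremarkable checks would be taken as reassurance about a contrast that is in fact biased.

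**Working it through.** **The plan's own figure.** The protocol's required numbers match completers divided by 0.75. For MVPA, 600 / 0.75 = 800; for fruit and vegetables, 250 / 0.75 = 333.3, rounded up to 334. The completer counts are back-calculated. No stated figure is disputed.

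**Size of the bias.** Let m be the share missing in an arm, and d the true mean of its non-responders minus the mean that a MAR analysis assigns them. The error in a mean difference has size |m_I·d_I − m_C·d_C|, which is 0.25 × |d_I − d_C| when 25% are missing in each arm.

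- If intervention non-responders do 60 min/week less MVPA than imputed and controls do not depart (assumed), the error is 0.25 × 60 = 15 min, half the 30-minute minimal effect.
- The protocol gives no SD. With 300 completers per arm, 80% power and an assumed two-sided 0.05, the implied MVPA SD is 30 / (2.8016 × √(2/300)) = 131. An arm difference in d of 0.4 SD gives 0.10 SD = 13.1 min, or 44% of the minimal effect. The standard error is √(2/300) = 0.0816 SD, so the shift is 1.22 standard errors and the type I error is 23%.
- An error as large as the whole minimal effect needs 30 / 0.25 = 120 min/week for MVPA, or 3 / 0.25 = 12 drinks/week for alcohol. These are large departures.

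**What the attempts check detects.** Simulation: 1,500 trials per pattern, 800 recruited, 1:1, no true effect except as noted, normal outcome with SD 1, 25% missing in each arm. Eight contacts were assumed (one text, two reminders, five calls), with cumulative response 30, 42, 50, 58, 64, 69, 72 and 75%. Dependence is the correlation between outcome and latent lateness.

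| Pattern | Size of bias (SD) | Attempts check rejects | Arm-by-attempts term rejects |
|---|---|---|---|
| Same in both arms, 0.2 | 0.00 | 87% | 5% |
| Intervention arm only, 0.2 | 0.09 | 33% | 32% |
| Intervention arm only, 0.3 | 0.13 | 62% | 61% |
| Opposite, ±0.2 | 0.17 | 5% | 86% |
| Opposite, ±0.1 | 0.08 | 4% | 31% |
| Intervention never-responders shifted 0.4 | 0.10 | 5% | about 5% |
| Intervention never-responders shifted 0.8 | 0.20 | 6% | about 5% |

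In the last two rows the shift itself creates a true contrast of 0.10 or 0.20 SD, which the MAR analysis misses. With ±0.2 the MAR contrast is falsely significant in 54% of trials. At 334 recruited, the one-arm rejection rates of the attempts check fall to 16% and 29%.

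The baseline check rejected in about 5% throughout. That is by construction, since the simulated baseline variable was unrelated to response. The case against it as a test of MAR is the logical one above.

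**Where a common departure matters.** By *Models*, alcohol, heavy episodic drinking and sugary drinks use negative binomial regression and smoking uses logistic regression: four of the six primary outcomes. Take assumed responder means of 7 v 10 drinks, ratio 0.70. If non-responders in both arms drink 4 more, the means become 7 + 0.25 × 4 = 8 and 10 + 0.25 × 4 = 11, ratio 0.73. A common departure also biases a mean difference if attrition differs by arm.

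**Smoking.** Assume 18% v 8% abstinent among responders and count all missing as smoking.

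- Equal 25% attrition: 0.18 × 0.75 = 13.5% and 0.08 × 0.75 = 6.0%, a difference of 7.5 points. The odds ratio moves from (0.18/0.82)/(0.08/0.92) = 2.52 to (0.135/0.865)/(0.060/0.940) = 2.45.
- Attrition 30% v 20%: 0.18 × 0.70 = 12.6% and 0.08 × 0.80 = 6.4%, a difference of 6.2 points and an odds ratio of 2.11.

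**The case against.** The strongest reply has four parts.

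1. The article does not say that the attempts regression pools the arms; it only omits an arm term. An analysis plan may add one, and may contain an MNAR analysis. This stands: the absence of an MNAR analysis from a condensed protocol is not itself a fault. What can be judged is the pair of checks the protocol does name.
2. A reader might infer that the checks cannot detect any failure that would bias the contrast. The documents and figures do not support that. On the protocol's own late-responder reasoning, the attempts check has about 16 to 62% power in the one-arm patterns. It detects a common departure well at 800 recruited, and such a departure biases ratio-scale contrasts and contrasts with unequal attrition. Its near-total blindness to opposite slopes comes from exact cancellation, a special case.
3. The protocol says it will explore MAR, not verify it, and no analysis of observed data can separate MAR from MNAR. This also stands. An interaction term gains nothing when one arm alone departs (32% v 33%) or when only never-responders differ.
4. The protocol's *Limitations* already acknowledges telephone follow-up as a risk of detection bias, and a web/telephone indicator is nearly determined by attempt number. Adjusting for it would remove much of the early-versus-late comparison. The acknowledgement, however, does not extend to how the attempts regression is to be read.

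It is also fair that the baseline comparison has value. It can show where the adjustment set in *Models* omits a predictor of response.

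**Conclusion.** The concern holds in limited form. By the protocol's own statement both planned analyses rest on MAR, so agreement between them would not test it. The baseline comparison does not bear on MAR against MNAR. The attempts regression is useful for a common departure, weak for a one-arm departure, and uninformative for opposite departures that cancel or for departures confined to never-responders; it also mixes lateness with mode.

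For a mean difference the consequence is 0.25 times the arm difference in departure. The figures rest on assumptions: equal 25% attrition by arm, an implied SD, a chosen response curve, five attempts read as five calls, and chosen departures. They show what the checks could pass over, not what will happen. The change is worth making because it improves an analysis already specified, at little cost.

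**What to change.** - Fit the attempts regression with arm and an arm-by-attempts term, and report both the common slope and the interaction.
- Interpret it with the change of mode in mind, for example by repeating it within the web attempts, and do not rely on a mode indicator. The web-only version covers a shorter range of attempts and has less power.
- State that the baseline comparison serves to choose imputation predictors.
- Because no check on observed data can rule out MNAR, add a supportive delta-adjusted version of the planned multiple imputation, with separate deltas per arm over a stated range, reported on each outcome's model scale. Counting missing as smoking can be one optional extreme scenario for abstinence.

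The cost is analysis-plan wording and reruns of an imputation already planned. The downside is a few extra supportive results to report and explain.

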## Methods

A 2-arm parallel groups single blind randomised controlled trial (1:1) will be employed to estimate the effectiveness of the novel intervention. A flow diagram of the trial design can be found in Fig. 1, and a trial participant timeline is presented in Fig. 2. This protocol follows the SPIRIT guidelines [27].

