#### Power calculations

Considering the novelty of the intervention (digital multiple lifestyle) and the population (Swedish high school students), there are no existing full-scale trials from which an estimate of effects can be assumed. Also, as there are no interventions of this type available to high school students in Sweden, minimal relevant effect sizes were considered for this trial. We have based expected effect sizes on what we believe are minimally relevant for the population, and reasonable, given the target population and digital intervention context. For those included based on weekly alcohol consumption, who drink 10 or more standard drinks per week, we believe a minimal relevant effect size to be a difference in means at follow-up of 3 standard drinks per week. Similarly, those who are included based on having one episode of heavy episodic drinking per month, a minimal relevant difference at follow-up would be 0.3 less episodes on average per month (or about 1 per 3 months). For physical activity, participants are included if they have less than approximately 60 min of MVPA per day, for which a mean difference at follow-up of 30 min per week (i.e., 5 min per day) would be a minimal effect size of importance in this group. Following the same reasoning as above, among those included based on eating less than 500 g of fruit and vegetables on average per day, we believe a minimal relevant effect size to be a difference in means of 0.5 portions per day (50 g per day). Among those included based on sugary drinks consumption (3 or more drinks per week), we believe that a mean difference of 2 drinks per week at follow-up represents a minimal effect size. Finally, for smoking, we rely on data from a text message smoking cessation which was evaluated among Swedish high school students, suggesting that we may expect approximately 10% less smokers in the intervention group.

Using the minimally relevant effect sizes described above, we conducted a Monte Carlo study to guide recruitment. The study was designed to identify the necessary number to recruit for each of the six outcomes in order to achieve a power of 80% at the 0.05 significance level. Recruitment will continue until each of the six outcomes have been powered (no more than 24 months). All assumed effects were allowed to vary during the Monte Carlo simulations, following a normal distribution with a standard deviation of 0.025.

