Based on attrition observed in a previous trial of a digital smoking cessation intervention in this population [61], we assumed 25% attrition to follow-up. We found that we will require 267 individuals for weekly alcohol consumption, 534 for heavy episodic drinking, 734 for sugary drinks, 334 for fruit and vegetables, 800 for MVPA, and 467 for smoking. Thus, we will recruit until all of these number have been achieved (or 24 months have passed). Using data from surveys on Swedish high school students’ health behaviour, we found that this will likely require the recruitment of 2000 students to the trial, although correlations among behaviours may reduce this overall number.

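### As written, data points judged erroneous leave only the sensitivity analysis, so one gross input error could outweigh the target effect on a numeric primary outcome

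*Protocol article*

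**What the plan says.** The only rule on data errors stands in the Statistical analysis section of the protocol article. The data are to be inspected on plots, and "sensitivity analyses will be performed excluding any erroneous data points". The check looks for two things, outliers and input errors, and the exclusion covers only points judged erroneous. That exclusion is assigned to sensitivity analyses. The article nowhere says that errors are queried, corrected or removed before the main analysis, and it does not define an erroneous point.

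The outcomes concerned are self-reported numbers (section on primary and secondary outcome measures). Under Models, MVPA and average fruit and vegetable intake go into normal regression with an optional log transform. Weekly alcohol, heavy episodic drinking and sugary drinks go into negative binomial regression. Smoking abstinence is binary and goes into logistic regression.

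**The concern.** The usual order is the reverse. A value known to be wrong is corrected or set to missing in the main analysis, and the sensitivity analysis asks whether that handling mattered. Here the primary estimate would carry the known error and the sensitivity analysis would carry the cleaned result.

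Neither normal regression on the raw scale nor a negative binomial model bounds the influence of one extreme value on a mean. A unit slip is also easy to foresee: fruit and vegetables are asked in portions of 100 g, while the inclusion criterion is in grams. At stake are the size, and possibly the sign, of a primary estimate and the width of its interval.

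**Working it through.** **Inputs from Power calculations.** The design aims "in order to achieve a power of 80% at the 0.05 significance level", and "we assumed 25% attrition to follow-up". The required totals are given as "we will require 267 individuals for weekly alcohol consumption, 534 for heavy episodic drinking, 734 for sugary drinks", and "334 for fruit and vegetables, 800 for MVPA, and 467 for smoking". Allocation is 1:1.

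**The plan's totals.** Evaluable totals of 200, 400, 550, 250, 600 and 350, divided by 0.75 and rounded up, give 267, 534, 734, 334, 800 and 467. These match the article. Completers per arm are therefore 100 (alcohol), 200 (heavy episodic drinking), 275 (sugary drinks), 125 (fruit and vegetables), 300 (MVPA) and 175 (smoking).

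**Implied SDs.** The article gives no SDs, so they are back-solved, assuming a two-sided test: SD = d × √(n/2) / 2.8016, where d is the target difference and n the completers per arm.
- MVPA: 30 × √150 / 2.8016 = 131 min.
- Fruit and vegetables: 0.5 × √62.5 / 2.8016 = 1.41 portions.

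**Size of a single error that equals the target.** One wrong value shifts its arm mean by error / n, so the break-even error is n × d.

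| Outcome | n per arm | Target d | Break-even error |
|---|---|---|---|
| Weekly alcohol | 100 | 3 drinks | 300 drinks |
| Heavy episodic drinking | 200 | 0.3 episodes | 60 episodes |
| Sugary drinks | 275 | 2 drinks | 550 drinks |
| Fruit and vegetables | 125 | 0.5 portions | 62.5 portions |
| MVPA | 300 | 30 min | 9,000 min |

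**MVPA, one entry of 10,000 min** (assumed true value 250; a week has 10,080 min).
- Shift: (10,000 − 250) / 300 = 32.5 min, above the 30 min target.
- SE without error: 131 × √(2/300) = 10.7.
- SE with error: √[(2 × 131² + 9,750²/300) / 300] = 34.2.
- Simulated t test with arm means 250 and 280: power about 0% if the error is in the control arm (mean estimate about −2 min), and about 33–34% if it is in the intervention arm (mean estimate about 63 min).

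**MVPA, 3,000 entered for 300.**
- Shift: 2,700 / 300 = 9 min, under a third of the target.
- SE: √[(2 × 131² + 2,700²/300) / 300] = 14.0.
- Simulated t test: power about 25% if the error is in the control arm, and about 86% with the estimate inflated to about 39 min if it is in the intervention arm.

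**Fruit and vegetables, 300 entered for 3** (grams typed as portions).
- Shift: 297 / 125 = 2.38 portions, or 4.75 times the target.
- Simulated t test: power about 0% with the error in either arm. With the error in the control arm the estimate is about −1.9 portions; a random-intercept model gives the same.
- With that one value set to missing instead (124 against 125 per arm), power is 79.8%.

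**Weekly alcohol, negative binomial model, 10 entered as 1,000 in the intervention arm** (means 10 and 7 assumed). The average rate ratio moves from 0.71 to 1.70, so the count model gives no protection.

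**Log scale.**
- MVPA, 10,000 for 250: ln(40)/300 = 0.012 against a target of ln(280/250) = 0.113, about 11% of it.
- Fruit and vegetables, 300 for 3: ln(100)/125 = 0.037 against ln(3.5/3) = 0.154, about 24% of it.

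**Smoking.** One wrong binary answer moves an arm by at most 1/175 = 0.6 percentage points, against a target of about 10.

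**The case against.** The strongest reply is that the article never says outright that known errors are kept. It is one sentence in a condensed article, and routine cleaning, range checks and queries commonly sit in an analysis or data-management plan that is not shown. This stands in part: a missing list of plausibility limits is no fault of the article. But the sentence does more than leave a gap. It places the exclusion in the sensitivity analysis, and that would have no purpose if the errors had already gone.

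The planned models also differ from a t test on raw minutes. The log transform is optional, the Bayesian models carry standard normal priors that could shrink the estimate (not modelled here), and the online form may block impossible entries. All of this stands as a limit on the size. It does not remove the point, because the log transform is only a possibility, maximum likelihood estimates without the priors also serve for inference, and the protocol itself expects input errors. A value of 10,000 minutes would be conspicuous on a plot, but under the stated rule spotting it does not remove it from the primary analysis. Both results would presumably be reported, so the influence would be visible.

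Three stronger readings are tempting but not supported:
- *Errors and genuine outliers are treated alike.* Both are looked for, but only erroneous points are excluded, so genuine extremes already stay in.
- *The check is done with knowledge of arm.* The article does not say so; its Randomisation section says research personnel are blind to allocation, and the detail belongs in an analysis plan.
- *One error cuts power to a single lower figure.* Holding the difference at 30 minutes and inflating only the SE gives 14% for the 10,000 entry and 57% for the 3,000 entry. Both figures ignore that the error moves the difference. Power depends on the arm, and for the milder slip it can rise while the estimate is biased.

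**Conclusion.** The point holds as a fault in a stated rule that should be corrected. Followed as written, values judged to be input errors remain in the primary analysis. For the five numeric primary outcomes on the raw or count scale, a gross error in one record can equal or exceed the target effect: 32.5 minutes against 30 for MVPA, and 2.4 portions against 0.5 for fruit and vegetables. A reader might infer that any typing slip would do this. It would not: a tenfold MVPA slip shifts the mean by about 9 minutes, and the direction of the bias depends on the arm.

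The figures rest on SDs implied by 80% power, two-sided testing at 0.05, 25% attrition and assumed typical values of 250 to 300 minutes, 3 portions and 10 drinks. They shrink greatly under a log transform and do not apply to smoking abstinence.

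**What to change.** Reword the one sentence in Statistical analysis along these lines:
- Before unblinding, set plausibility limits for each numeric outcome (for example, MVPA not above the minutes in a week) and apply them blind to arm.
- In the primary analysis, correct confirmed or impossible values where the true value can be established. Otherwise set them to missing and handle them with the multiple imputation already planned.
- Keep extreme but possible values in the primary analysis.
- Report a sensitivity analysis that uses all recorded values.

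The cost is a few lines of text and a handful of values that become missing. No new data are needed.

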### Study setting, recruitment and eligibility

Participating high schools (approximately 300 high schools with approximately 80,000 students in total) will recruit students to the trial using: printed advertising (posters and leaflets), digital advertising (email, school website, app), and school staff (teachers, mentors, and/or school health centers). Participants will initially be recruited over a 6-month period, with additional 3-month periods added until the required number of participants has been reached (see Power Calculations). Recruitment will not extend past 24 months, regardless of number of participants recruited, and will commence in September 2020.

Students will register their interest by sending a text message to a dedicated telephone number (included in all information materials). In response, students will receive a text message with a hyperlink to a web page presenting trial information and will be asked to give informed consent to participate. All students who consent will immediately be asked to complete an online baseline questionnaire (see Additional file 1), which will also be used to assess eligibility for the trial.

Students will be included in the trial if they fulfil at least one of six conditions, which are related to the primary outcomes of the trial. The conditions are:
**Weekly alcohol consumption:** Consumed 10 or more standard drinks of alcohol the past week. A standard drink of alcohol is in Sweden defined as 12 g of pure alcohol.**Heavy episodic drinking:** Consumed 4 or more standard drinks of alcohol on a single occasion at least once in the past month.**Fruit and vegetables:** Consumed less than 500 g of fruit and vegetables on average per day the past week.**Sugary drinks:** Consumed 3 or more units of sugary drinks the past week. One sugary drink unit is defined as approximately 33 cl.**Moderate to vigorous physical activity:** Spent less than 420 min on moderate to vigorous physical activity in the past week (ie. approximately 60 min per day).**Smoking:** Having smoked at least one cigarette the past week.

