### Models

#### Primary and secondary outcomes

Analyses of primary outcomes will be conducted among those fulfilling the respective criteria for inclusion at baseline, for example weekly alcohol consumption will be analysed among those who reported having consumed 10 or more drinks of alcohol in the past week. BMI and candy/snacks will be analysed among all participants, and number of cigarettes smoked weekly among baseline smokers.

Weekly alcohol consumption, frequency of heavy episodic drinking per month, weekly intake of candy and snacks, number of sugary drinks per week, and cigarettes smoked per week are all count variables that are likely skewed and overdispersed. Therefore, these outcomes will be analysed using negative binomial regression. If found not to be overdispersed, we will consider using normal regression (possibly log transformed). Average intake of fruit and vegetables per day, MVPA minutes per week, and BMI will be analysed using normal regression (possibly log transformed). Point prevalence of smoking abstinence will be analysed using logistic regression.

All models will be adjusted for sex, age, family’s economic situation, and mediator variables at baseline. Effect modification will be investigated by estimating the outcome models with interaction terms for each baseline variable respectively. To further investigate effect modification with respect to socioeconomic status, we will estimate the outcome models with both education and economic status as interaction terms. A final effect modification model will be estimated with a binary interaction variable representing age being greater to or equal to 18 (ie. drinking age).

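### The effect is read from group-by-time coefficients: under the usual coding this can favour the intervention for smoking when the arms are identical, and the covariate list leaves out the baseline outcome

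*Protocol article*

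**What the plan says.** The Statistical analysis section specifies "multilevel models with adaptive intercepts (per individual) and time by group interactions" and says where the effect is read: "For each group by time coefficient, we will report the marginal posterior probability of effect". The posterior median of that coefficient is the effect size. On priors it says "Bayesian inference will be used to estimate the parameters of the models [54–57] with standard normal priors". The Bayesian fit is accompanied by "maximum likelihood estimates and null hypothesis test at the 0.05 significance level", and both sets of estimates are to be used for inference.

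The section Primary and secondary outcomes fixes the analysis sets: "Analyses of primary outcomes will be conducted among those fulfilling the respective criteria for inclusion at baseline". It also fixes the covariates: "All models will be adjusted for sex, age, family’s economic situation, and mediator variables at baseline". The baseline value of the outcome is not among them. Smoking abstinence is analysed by logistic regression.

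The entry criterion that defines the smoking set is "Having smoked at least one cigarette the past week". Follow-up is at 2 and 4 months. The article does not say whether baseline is a row of the longitudinal outcome, whether the model has a separate group main effect, or how group is coded.

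**The concern.** A group-by-time coefficient equals the treatment effect only under some parameterisations. The article names the coefficient as the reported quantity but not the parameterisation.

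The matter is sharpest for smoking. Everyone in that set smoked in the week before entry, so abstinence is 0% in both arms at baseline, whether the look-back is one week or four. A model that includes this visit and gives it its own group term must fit an infinite baseline log-odds in each arm. Maximum likelihood cannot do that, and a standard normal prior resists it. At stake is a reported probability of benefit, for one of six primary outcomes, that owes more to the priors and coding than to the data.

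For the other outcomes the question is smaller: whether precision is lost by leaving out a baseline value that the eligibility questionnaire already collects.

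**Working it through.** **Inputs.** The article requires 467 smokers with 25% attrition. 467 reproduces as 350 / 0.75 = 466.7, rounded up, so 175 evaluable per arm. The 350 itself cannot be reproduced, because no control abstinence rate is given. Reading the expected effect as 10 percentage points (two-sided 0.05, 80% power), the recruitment figure is 456 at 7.5% control abstinence and 472 at 8%, so about 8% would fit. I take 8%, 20% and 35% as assumed rates.

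**Reading A: baseline is a row, with a group main effect and 0/1 coding.** The log-odds of abstinence are a + b·G + t2·T2 + t4·T4 + g2·G·T2 + g4·G·T4. The reported coefficient is g4; the arm contrast at month 4 is b + g4.

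*Maximum likelihood.* Baseline is 0/175 in each arm, so a and b have no finite estimate, and g4, measured against b, has none either. Take 14/175 v 32/175 at follow-up. The direct log odds ratio is ln[(32/143)/(14/161)] = 0.945, with SE √(1/32 + 1/143 + 1/14 + 1/161) = 0.34, a ratio of 2.8. In the model with the baseline row, the software's SE for the interaction is about 33,000, so the coefficient cannot reach significance.

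*Bayesian.* N(0,1) on every coefficient, no random intercept, no covariates, identical arms (0/175 at baseline, the same count in both arms at months 2 and 4):

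| Abstinent, both arms | g4 median | Pr(g4 > 0) | b + g4 median | Pr(b + g4 > 0) |
|---|---|---|---|---|
| 14/175 (8%) | +0.70 | 0.90 | -0.01 | 0.49 |
| 35/175 (20%) | +0.82 | 0.95 | +0.01 | 0.52 |
| 61/175 (35%) | +0.89 | 0.97 | +0.02 | 0.54 |

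The arm coded 1 has an extra coefficient with which to fit its empty baseline. So b goes negative (-0.81 at 20%) and g4 goes positive by about the same amount. A wide intercept prior (SD 5) reduces this at 20% to +0.66 and 0.90.

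With the random intercept that the article specifies (half-normal(0,1) prior on its SD assumed, about 467 smokers, 25% missing at each follow-up), the shift is somewhat larger: +0.95 and 0.97 at 20%. In simulated trials with no effect, Pr(g4 > 0) exceeded 0.975 in 50% of 150 trials at 20% abstinence and in 15% of 300 trials at 8%. The arm contrast b + g4 exceeded it in 2% and 1%.

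**Reading B: only months 2 and 4 are rows, with a group main effect.** The effect is b at month 2 and b + g at month 4, so g is the change in effect. With 20% v 30% abstinent at both visits, b = ln[(0.30/0.70)/(0.20/0.80)] = 0.54 and g = 0. A steady benefit would be reported as none.

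**Reading C: one group-by-time coefficient per follow-up, no group main effect.** Each coefficient is then the arm contrast at its visit. With a baseline row and identical arms, the month-4 coefficient is about +0.08 to +0.10, with probability 0.60 to 0.64. In 400 null trials (normal approximation, no random intercept), probability exceeded 0.975 in 3% at 8% abstinence and 7% at 20%, against 13% and 27% for Reading A fitted the same way.

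**Other outcomes.** A simulated continuous outcome was selected on a baseline below 420. Change score, follow-up only and baseline-adjusted analysis (ANCOVA) all showed no bias and type I error of about 5%. The SEs were:

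| Baseline correlation | Change score | ANCOVA | Ratio |
|---|---|---|---|
| 0.3 | 17.5 | 15.5 | 1.13 |
| 0.5 | 15.3 | 14.3 | 1.07 |
| 0.7 | 12.4 | 11.7 | 1.06 |

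In power terms, suppose a comparison of follow-up means has 80% power (z = 2.80). With k the ratio of baseline to follow-up SD, a change score has power Φ(2.80/√(1 + k² - 2ρk) - 1.96), and ANCOVA Φ(2.80/√(1 - ρ²) - 1.96).

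- ρ = 0.3: change 66% at k = 1, 77% at k = 0.7, 82% at k = 0.5; ANCOVA 84%.
- ρ = 0.5: change 80%, 88%, 90%; ANCOVA 90%.

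**The case against.** The strongest reply is that the article does not commit to the harmful model. Reading C is a common constrained-baseline model for randomised trials, fits the wording, and largely avoids both problems. Coding group as ±0.5 also removes the artefact under Reading A (probability 0.50). Such details are often left to a full analysis plan, which is not shown. This stands: the smoking result is conditional. But the article does fix the reported quantity, and under the usual coding that quantity is wrong for smoking with either choice of rows.

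A reader might go further in four ways that the document does not support.

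- *The plan will manufacture a smoking effect.* It can, under Reading A; that model is not stated. The size also varies with assumed abstinence and with the random intercept.
- *Selecting on baseline biases the other five outcomes.* Selection precedes randomisation and acts equally in both arms. The check found no bias.
- *The test addresses a different target from the one powered.* The Power calculations section speaks, for example, of "a difference in means at follow-up of 3 standard drinks per week". Under randomisation, the expected difference in change equals the expected difference in follow-up means for a continuous outcome; only precision differs. Truncation at entry also tends to shrink the baseline SD, which reduces the loss.
- *There is no adjustment for baseline at all.* That is exact only for the covariate list. If baseline is a row, the individual intercept adjusts for it in part.

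**Conclusion.** The point holds in a conditional form. Naming the group-by-time coefficient as the effect is unsafe for smoking. With baseline as a row and a 0/1-coded group main effect, it has no maximum likelihood estimate, and with identical arms its posterior sits at about +0.7 to +0.9 log-odds with probability of benefit about 0.9 to 0.97. Those figures assume 175 per arm, 8% to 35% abstinence, N(0,1) on every coefficient and no random intercept. With months 2 and 4 only and a group main effect, it measures the change in effect rather than the effect. A model without a group main effect is largely free of both faults, but the article does not specify it.

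For the other five primary outcomes the issue is efficiency, not validity: in the continuous example, an SE about 6% to 13% larger for a change score than for ANCOVA, with less power lost if the baseline SD is smaller than the follow-up SD. The count outcomes were not simulated.

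**What to change.** State that the 2- and 4-month values are the outcomes, and that the effect is the arm contrast at each visit (with a group main effect, b at month 2 and b + g at month 4), not the raw interaction coefficient. Attach the posterior probability, median, intervals and maximum likelihood test to those contrasts.

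Add the baseline value of the same outcome to the covariate list for the count and continuous outcomes. For smoking, baseline abstinence is constant and cannot be a covariate; use baseline cigarettes per week if the baseline questionnaire collects it, which the article alone does not show.

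The cost is a change of analysis wording. Eligibility screening already collects baseline values for the five other primary outcomes, and recruitment and follow-up are unaffected.
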